### Design and Settings

First, patients will be recruited in a baseline phase lasting 4 months to observe usual care without using the DA. It means that oncologists will inform patients about further treatment options for cancer-specific therapy, side effects, and potential benefit, but they will not explicitly address that best supportive care would also be an option and will not use a decision support tool for eliciting patient preferences and assisting in decision making. The baseline phase will be followed by an intervention phase lasting 6 months. Oncologists and patients will use the DA in the same situation (change of treatment needs to be discussed with the patient because of disease progression, treatment toxicity, or other reasons). A minimum of 40 doctor-patient encounters will be included in the 4-month baseline, and 40 doctor-patient encounters will also be included in the 6-month DA intervention phase. The whole sample will encompass 80 doctor-patient encounters. The planned sample size is largely determined by the feasibility of recruiting patients within the available project duration.

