### Measurements

The potential effect of the DA will be evaluated by testing the improvements on the primary outcome for our study level of decisional conflict. Level of decisional conflict will be measured with the Decision Conflict Scale [55] that assesses patients’ perceptions of uncertainty, modifiable factors contributing to uncertainty, and ultimate satisfaction with the choice. It is one of the most robust and validated instruments to test the impact of DAs in end-of-life decision making [56]; We assume that the Decisional Conflict Scale score will decrease for the patients who use the DA.

Furthermore, we aim to assess the patients’ involvement in decision making, certainty about choice, and satisfaction with the oncologist-patient interaction as exploratory endpoints. Patients’ involvement in decision making will be assessed with the German questionnaire on shared decision making (PEF-FB-9) [57]. The trade-off between patients’ preferences for quality and length of life will be assessed with the validated German version of the Quality-Quantity Questionnaire [1]. The preferred role of the patient in decision making will be assessed with the German version of the Control Preference Scale [58]. Satisfaction with the oncologist-patient interaction will be assessed using the validated Questionnaire on the Quality of Physician-Patient Interaction (QQPPI) [59]. Effect on hope (German version of the Herth Hope Index [60]), anxiety (EQ-5D-5L [61]), quality of life (EORTC QLQ-C30 [62]), and documentation of patient preferences will be measured.

Description of the measures and their psychometric properties, scoring, and interpretation are provided in Table 1.

Such determinants of quality of palliative care as time of integration of specialized palliative services into care, aggressiveness of therapy (anticancer treatment <14 days before death), and place of death will be recorded.

During data collection, patients might have changes in mental status (ie, develop depression or cognitive problems) as well as experience changes in decision making. The study physician involved with data collection will document all possibly relevant factors.

The questionnaires will be completed by patients and oncologists before and after the intervention and will take approximately 15-20 minutes to complete. All assessments will be conducted in German.

**Table 1 table1:** Description of the measures and their psychometric properties, scoring, and interpretation.

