### Sample Characteristics

Patients will be recruited at participating study sites (Jena, Heidelberg) in inpatient and outpatient settings. Patients will be identified by a study nurse via the electronic health record of patients scheduled in the outpatient or inpatient clinic and approached for participation if they fulfill the inclusion criteria.

We will include adult patients with incurable, stage IV disease (prostate, breast, pancreatic, stomach, or colorectal cancer) in an advanced treatment stage (prognosis <12 months or standard palliative care only is considered). The patient must have an adequate level of the German language to complete the questionnaire and is willing and able to give informed consent for participation in the study.

We will exclude patients from the study who are already under standard palliative care only, are cognitively impaired, have extreme anxiety or distress, or have a severe comorbid illness, excluding antitumor treatment as assessed by the treating oncologist.

The influence of implicit bias will be reduced by recruitment of patients both in Heidelberg and Jena. In addition, the use of a trained study nurse at both sites will reduce implicit bias in recruitment. Drop-out reasons will be documented.

Oncologists will be recruited from the participating study sites (Jena, Heidelberg). They will be identified by a study nurse and invited to participate in the study via phone. We will include oncologists with different levels of working experience and of varying ages. The oncologists who participated in the development of the DA will be excluded from participation in the study.

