### Data Analysis

Analyses will be performed using SPSS v.20.0. A descriptive analysis of the sample will be performed. According to the level of variables, means, SDs, medians, minimum and maximum, and absolute or relative frequencies will be reported.

Clinically significant decisional conflict will be calculated and defined by a score of ≥25/100 on the Decision Conflict Scale, which is the most commonly used threshold to distinguish a harmful level of decisional conflict [62-64].

We will compare primary and exploratory outcome measures between the 2 patient groups (baseline and intervention) using Student *t* tests or analysis of variance. Parametric or nonparametric statistics (depending on the distribution of the data) will be used for the analysis of the patient groups from the baseline and intervention phases.

We will compare clinical confounders (time of integration of specialized palliative services into care; aggressiveness of therapy [anticancer treatment <14 days before death and place of death]) between the 2 patient groups (baseline and intervention) by comparing mean values. Measures of variability (SD) will be calculated.

Given the practice-based character and the small sample size of the study, we refrain from extensive measurement and multivariate analysis of mediators and moderators of the intervention effects. For the latter reason, we do not plan to use multiple imputation of missing values. Missing values will be handled by allowing a maximum of 35% missing in the calculation of scale scores.

*P* values of the corresponding statistical tests comparing treatment groups (ie, 2-sample *t* tests for continuous variables and chi-square tests for categorical data) will be given. Statistical significance will be assessed at the level of α=.05 (two-sided).

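### For the three late palliative-care and end-of-life outcomes, the comparison by phase can be biased toward no difference, because baseline patients may meet the decision aid after the switch and no stated rule prevents or records it

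*Protocol article*

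**What the plan says.** All references are to the Protocol article, Methods.

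- **Order of phases** (Design and Settings): "First, patients will be recruited in a baseline phase lasting 4 months to observe usual care without using the DA". Then: "The baseline phase will be followed by an intervention phase lasting 6 months". No gap between the phases is described.
- **Trigger for the DA** (Design and Settings): "Oncologists and patients will use the DA in the same situation (change of treatment needs to be discussed with the patient". The trigger is a clinical situation, and no exception is made for patients enrolled at baseline.
- **Unit and size** (Design and Settings): "A minimum of 40 doctor-patient encounters will be included in the 4-month baseline, and 40 doctor-patient encounters will also be included". The unit is the encounter.
- **Exclusions** (Sample Characteristics): "We will exclude patients from the study who are already under standard palliative care only, are cognitively impaired, have extreme anxiety or distress". Severe comorbid illness completes the list; earlier participation is not on it. Eligible patients have a prognosis below 12 months or are being considered for palliative care only.
- **Late outcomes** (Measurements, pre-post study): the timing of specialist palliative services is listed, and "aggressiveness of therapy (anticancer treatment <14 days before death), and place of death will be recorded".
- **Comparison** (Data Analysis): "We will compare clinical confounders (time of integration of specialized palliative services into care", followed by the other two items, between the baseline and intervention groups.
- **Questionnaires** (Measurements, pre-post study): patients and oncologists complete them before and after the intervention.

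**The concern.** The comparison by phase treats baseline patients as having had no DA. For an outcome measured at the encounter this is true by construction, because baseline encounters come before the DA is in use. The three chart-based outcomes are different. Two are known only at death, and the third may occur months after enrolment. A baseline patient who survives the switch and reaches another treatment-change discussion is in exactly the situation that calls for the DA in the second phase.

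If that happens, the contrast for these outcomes is between the DA now and the DA possibly somewhat later, and a real effect is pulled toward zero. This matters because the Conceptional Framework section suggests the DA may reduce intensive treatment, and the pre-post study section names clinical outcomes among its aims and uses the observed effects to inform the size of a definitive trial. Without a record of later DA use, the dilution would be hard to recognise afterwards.

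**Working it through.** **Plan's own figure.** 40 + 40 = 80, which matches: "The whole sample will encompass 80 doctor-patient encounters". The Abstract says 70; that is a separate discrepancy and does not affect the shares below.

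**Inputs from the document.** Baseline phase, months 0-4. DA phase, months 4-10. The study window of October 2021 to September 2022 gives about 12 months. There are 40 baseline encounters, taken here as 40 patients.

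**Assumptions (not in the document).** Uniform enrolment over months 0-4; exponential survival with median m of 4, 6, 9 or 12 months, chosen in view of the prognosis criterion; follow-up to month 12, with month 10 as a check. The article does not state how long the late outcomes are followed.

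**Formulas**, with h = ln 2 / m:

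- Alive at the switch: A = (1 − e^(−4h)) / (4h)
- Dead by month 12: D = 1 − (e^(−8h) − e^(−12h)) / (4h)
- Share of those deaths after the switch: S = (D − (1 − A)) / D

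Example, m = 6: h = 0.1155. A = (1 − 0.630)/0.462 = 0.801. D = 1 − (0.397 − 0.250)/0.462 = 0.682. S = (0.682 − 0.199)/0.682 = 0.708.

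| Median survival (months) | Alive at switch | Of 40 | Baseline deaths by month 12 falling after switch | Same, by month 10 |
|---|---|---|---|---|
| 4 | 72% | 29 | 66% | 63% |
| 6 | 80% | 32 | 71% | 67% |
| 9 | 86% | 34 | 74% | 70% |
| 12 | 89% | 36 | 76% | 71% |

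So in every scenario most baseline deaths, and with them the two death-based outcomes, fall in the period when the DA is in use or after it.

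**From survival to bias.** Let q be the share of those later decedents who meet the DA before death. If later use had the full effect of use at enrolment, the contrast among decedents would be (1 − q × S) times the true effect. With q = 0 there is no bias. With q = 1 the effect would shrink by S, that is by 66-76%, which is a ceiling. The document gives no value for q, so no point within this range can be preferred.

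**Encounter-based outcomes.** Baseline questionnaires are taken around an encounter that precedes DA use, so q does not enter. The exception is a patient who contributes encounters to both phases, which the text neither allows nor forbids. That would also violate the independence on which the planned 2-sample tests rest.

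**The case against.** A reader might infer that the baseline group is contaminated and that every DA effect, including that on decisional conflict, is diluted. The document does not support this. The primary outcome is measured around the encounter. Later exposure of baseline patients is nowhere stated. That the same oncologists serve both phases is an inference; the article says only that oncologists are recruited from the two sites.

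A reader might also attach a size, for example by assuming that 25-75% of later decedents meet the DA, which would put 17-57% of baseline decedents in the exposed group. That rate has no source in the document. It also sits uneasily with the design if DA use is confined to study encounters: about 13-22 of 40 baseline patients would die between months 4 and 12, and 75% of these would take up 10-16 of the 40 intervention encounters (25-40%).

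Other points on that side carry weight. Data Analysis speaks of two patient groups, which suggests separate patients. Baseline patients who have moved to palliative care only could not re-enter. The study physician is to document all factors that may be relevant. This is a pilot, and the late outcomes are secondary to its purpose. A condensed article may also leave operational rules to a fuller document.

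What remains is narrower. The article does state the trigger, the exclusions and the comparison, and as written they allow crossover for the late outcomes. The general sentence on documentation concerns mental status and decision making; it does not define a DA-exposure variable, and Data Analysis uses none.

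**Conclusion.** The point holds for three outcomes only: timing of specialist palliative services, anticancer treatment shortly before death, and place of death. For these, the comparison by enrolment phase can be biased toward no difference. Under the stated survival assumptions, about 72-89% of baseline patients are alive when DA use begins and about 66-76% of their deaths by month 12 come later. These figures show the opportunity for exposure, not its extent; the exposed share is unknown and may be small. The primary outcome and the other encounter-based questionnaires stand unless a patient is enrolled in both phases. Any difference between the groups in length of follow-up is a separate matter and is not counted here. The change is worth making before recruitment because analysts may be unable to repair the gap afterwards.

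**What to change.** - **Sample Characteristics:** state that a patient enrolled in the baseline phase is not enrolled again in the intervention phase. This also secures the independence of the two groups.
- **Measurements (pre-post study):** record for each baseline patient whether and when the DA was used after the switch.
- **Data Analysis:** keep the comparison by enrolment phase as the main analysis of the three late outcomes and report how many baseline patients were DA-exposed. Add a sensitivity analysis that censors exposed baseline patients at first DA use (timing of palliative services) or shows them separately (the two death-based outcomes).

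The sensitivity analysis should not replace the main one. Setting exposed patients aside leaves the earlier deaths. Censoring may be informative, because DA use is prompted by events such as progression or toxicity. Both limits should be stated with the results.

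Cost: one eligibility sentence, one chart variable and one additional analysis. The re-enrolment rule slightly narrows the pool for the intervention phase.

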**Methods:**

In the first step, we will assess patients’ information and decisional needs as well as the views of the health care providers regarding the content and implementation of the DA. Through a scoping review, we aim to analyze specific characteristics of the decision-making process and to specify the treatment options, outcomes, and probabilities. An interdisciplinary research group of experts will develop and review the DA. In the second step, testing of the DA (design and field testing) with patients and oncologists will be conducted. As a last step, we will run a pre-post design study with 70 doctor-patient encounters to assess improvements on the primary study outcome: patients’ level of decisional conflict. In addition, the user acceptance of all involved parties will be tested.

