### User Acceptance Testing With Oncologists and Patients

A variety of factors can affect users’ acceptance of a DA. Among these factors, users’ perceptions and expectations are the key factors that influence their acceptance. Therefore, we aim to survey the oncologists’ and patients’ acceptance of the DA. The acceptance testing will be conducted during the intervention phase with patients and oncologists who will be caring for the patients in the pre-post study. The major aim is to assess oncologists’ perceptions of the usefulness (how useful oncologists find the DA), willingness to use the DA in daily routine with patients (how comfortable they would be to use the DA with patients), willingness or readiness to use it in clinical practice (how likely they would use it within the next 5 months), and perceived need for the DA. In addition, the patients’ perceptions of usefulness and willingness to use the DA during consultations with their oncologists will be assessed. The oncologists who were involved in the development of DA will be excluded from acceptance testing.

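### The planned t and chi-square tests ignore that encounters share oncologists, so the true type I error may differ from 5% in a direction the article does not settle

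*Protocol article*

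**What the plan says.** Design and Settings describes two consecutive phases, 4 months of usual care and then 6 months with the decision aid (DA), and counts the sample in consultations: "A minimum of 40 doctor-patient encounters will be included in the 4-month baseline, and 40 doctor-patient encounters will also be included". It adds that "The whole sample will encompass 80 doctor-patient encounters". The size comes from practicality, not from a power calculation: "The planned sample size is largely determined by the feasibility of recruiting patients within the available project duration".

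Sample Characteristics says that oncologists are recruited from the Heidelberg and Jena sites and that those who helped develop the DA are excluded. It gives no number of oncologists, no limit on encounters per oncologist, and no statement that the same oncologists serve both phases. User Acceptance Testing refers to "patients and oncologists who will be caring for the patients in the pre-post study", so oncologists are participants with their own caseload in the study.

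Data Analysis compares the two groups with Student t tests or analysis of variance, or nonparametric alternatives, and specifies P values from "2-sample *t* tests for continuous variables and chi-square tests for categorical data" at a two-sided 5% level. No term for oncologist or site appears. The section declines multivariate analysis of mediators and moderators, which is a different matter from clustering.

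**The concern.** All the named tests treat the encounters as independent. That is doubtful here because the oncologist is part of the intervention. Under Development of a DA, the oncologist introduces the aid and personally adds the prognostic information. Conceptional Framework expects the aid to affect communication between provider and patient. One outcome rates the physician's interaction with the patient, another measures shared decision making, and the primary outcome, decisional conflict, arises from the same conversation. Patients of one oncologist are therefore likely to answer more alike than patients of different oncologists.

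Two things are at stake. First, the standard error of the phase difference may be too small or too large, so P values and intervals may not have their stated properties. Second, one stated objective of the pilot is to help determine the sample size of a definitive trial. If patients are nested in oncologists in that trial, it will need some idea of the ICC, and an analysis that ignores oncologists gives none.

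**Working it through.** **The plan's own figure.** 40 + 40 = 80, which agrees with Design and Settings. The Abstract differs ("we will run a pre-post design study with 70 doctor-patient encounters"), and the two totals should be reconciled separately. The check below uses 40 per phase. There is no effect size, SD or power figure to reproduce.

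**Inputs.** From the article: n = 40 encounters per phase; two-sided α = 0.05; tests without a cluster term. Assumed, because the article gives none of them:
- K = 4 to 20 oncologists per phase, with equal caseloads m = 40/K
- ICC ρ = 0.02 to 0.10
- a fraction f of oncologists who serve both phases, with stable effects

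**Formula.** With total variance 1, each phase mean has variance ρ/K + (1 − ρ)/n, and the two means have covariance fρ/K. The difference therefore has variance (2/n) × D, where

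D = 1 − ρ + (1 − f)mρ.

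For f = 0 this is the usual design effect 1 + (m − 1)ρ. For f = 1 it is 1 − ρ, below 1. An ordinary test takes D = 1, so its true type I error is about 2[1 − Φ(1.96/√D)].

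**Example.** K = 4, m = 10, ρ = 0.10:
- f = 0: D = 0.90 + 1.00 = 1.90; effective n = 40/1.90 = 21.1 per phase; error 15.5%
- f = 0.5: D = 0.90 + 0.50 = 1.40; error 9.8%
- f = 1: D = 0.90; error 3.9%

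**Results** (D, then type I error):

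| K | ρ | None shared | Half shared | All shared |
|---|---|---|---|---|
| 4 | 0.02 | 1.18, 7.1% | 1.08, 5.9% | 0.98, 4.8% |
| 4 | 0.05 | 1.45, 10.4% | 1.20, 7.4% | 0.95, 4.4% |
| 4 | 0.10 | 1.90, 15.5% | 1.40, 9.8% | 0.90, 3.9% |
| 8 | 0.02 | 1.08, 5.9% | 1.03, 5.3% | 0.98, 4.8% |
| 8 | 0.05 | 1.20, 7.4% | 1.075, 5.9% | 0.95, 4.4% |
| 8 | 0.10 | 1.40, 9.8% | 1.15, 6.8% | 0.90, 3.9% |
| 20 | 0.02 | 1.02, 5.2% | 1.00, 5.0% | 0.98, 4.8% |
| 20 | 0.05 | 1.05, 5.6% | 1.00, 5.0% | 0.95, 4.4% |
| 20 | 0.10 | 1.10, 6.2% | 1.00, 5.0% | 0.90, 3.9% |

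**Check by simulation.** The ordinary t test was applied to 20,000 null trials per setting. Rejection rates were about 0.05 to 0.16 with no shared oncologists, 0.05 to 0.10 with half shared, and 0.04 to 0.05 with all shared. If the same oncologists serve both phases but only 80% of the oncologist variance carries over, the rate is about 0.046 to 0.065.

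**The case against.** The strongest reply is that the phases run one after the other in the same two departments, so many oncologists probably serve both. In that case the plain t test is close to nominal or slightly conservative. The only ratio in the article, 4-6 oncologists for 16-20 patients in Field Testing, is 2.7 to 5 patients per oncologist. Carried over (an assumption), it gives about 8 to 15 oncologists per phase, not 4. The study also calls itself a pilot that explores potential effects, and no confirmatory decision rests on its P values. An ICC from so few oncologists would be imprecise.

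Much of this stands, and it rules out two stronger readings.

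- A reader might infer that the P values are wrong, with a false-positive rate near 16%. That figure needs four oncologists per phase, no overlap and an ICC of 0.10 together. The article supports none of the three, and substantial overlap is the more natural reading.
- A reader might infer that one patient can be counted several times, because the sample is counted in encounters and a change of treatment can recur. The article never says so. It speaks of recruiting patients and of two patient groups, which points to separate patients. Silence here calls at most for a clarifying sentence.

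What the reply does not remove is that the article names tests that assume independence, for data that share oncologists. It does not require the same oncologists, or equal caseloads, in both phases. Declining to analyse mediators and moderators does not address this.

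**Conclusion.** The point holds in a limited form. The tests fixed in Data Analysis are at their nominal 5% level only if encounters are independent or the oncologist effects happen to balance out. Under the assumed ranges the true level is about 4-5% with full, equal overlap of oncologists, about 5-10% with half overlap, and about 5-16% with none. The direction is not settled by the article, and the departure is small if oncologists are many, the ICC is low or overlap is high. These figures rest on assumed oncologist numbers, ICC and overlap, on equal caseloads, and on oncologist effects that are stable between phases. Because the study is exploratory, the consequence is unreliable precision and a missed chance to inform the definitive trial; it does not invalidate the study. The change is still worth making because it costs little.

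**What to change.** 1. Record an oncologist code on every encounter. State how many oncologists take part and whether they serve both phases.
2. Replace the plain t and chi-square comparisons with a model for phase that includes an oncologist effect: a random intercept with small-sample degrees of freedom, or fixed oncologist effects if the same oncologists serve both phases. Fixed effects cannot separate phase from oncologist if the oncologists differ. Use the logistic counterpart for binary outcomes.
3. Adjust for the pre-score, which Measurements already has collected, and for site.
4. Report the ICC with its confidence interval as a rough input for the definitive trial, and say that it will be imprecise.
5. As a clarification, state that each patient contributes one index encounter in one phase.

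The cost is one identifier per form, a slightly more complex analysis and possibly wider intervals. No additional patients or questionnaires are needed.
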